#### **4.5 Sample Size**

A sample size of 48 subjects (24 for each group) was calculated to test whether there is a minimum difference of 1 bowel movement/week between the mean bowel movements per week of the intervention and control groups at the last time point (week 12) of the repeated measures study (with the addition of 10% for possible losses and refusals, this number should be 54, 27 for each group). The calculation considered 80% power, a significance level of 5%, a standard deviation of 1.15 and 1.21 bowel movements/week for the intervention and control groups, respectively (Rusch et al., 2024). As well as 90% retention at time points 2 and a permutable correlation matrix with a correlation of 0.5. This calculation was performed using the PSS Health online tool (Borges et al., 2020).

#### **4.6 Procedures by groups**

The individuals included in the study will undergo the complete initial assessment (baseline) and will then be randomized into control or intervention groups. After randomization, participants will return to the CPC within 7 days (D0) for stool sample delivery, and participants in the intervention group will receive nutritional guidance.

At 45 days (D45), dietary intake and constipation will be assessed via telephone. At the end of the study (D90), participants will be called to return to the CPC for the complete final assessment. At this time, if positive, participants in the control group will receive complete nutritional guidance. The researchers responsible for the final assessment and data processing will be exclusive to these tasks and will not have access to randomization and group allocation information.

##### **4.6.1 Control group**

After the study period (D90), if the intervention shows benefits, the participants in the control group will receive printed material and guidance on healthy eating, fiber and fluid consumption, as well as information about the relationship between protein and dopamine. The intervention will be carried out in a waitlist format, ensuring that all participants benefit, even if at different times. This strategy aligns with the study's objective of evaluating the effect of a nutritional intervention with nutritionist monitoring, while also preserving the ethical principle of beneficence for everyone involved.

#### 4.6.2 Intervention Group

Participants allocated to the nutritional intervention group will receive complete nutritional follow-up, including a calculated meal plan, nutritional guidance, and support via telephone calls throughout the study.

##### **First Nutritional Consultation (D0)**

Based on the baseline assessments, a meal plan will be developed for each participant according to the proposed protocol below. In this first consultation, participants will receive guidance on: healthy eating and the level of food processing based on the Food Guide for the Brazilian Population (2014); sources of dietary fiber and the importance of adequate fluid intake; levodopa-nutrient interaction and the importance of the fasting period before and after taking the medication.

##### *Diet plan calculation protocol*

The meal plan will be calculated by a nutritionist on the DietBox © platform, using the Brazilian Food Composition Table (TACO) - 4th edition as the basis for food selection. The daily energy will be calculated based on the 2023 equation for Estimated Energy Requirement (EER) (Cominetti; Cozzolino, 2023).

For the calculation of daily protein, the Recommended Dietary Allowance (RDA) for healthy adults of 0.8 g PTN/kg/day will be used. The Protein Redistribution Diet (PRD) will also be implemented, which consists of restricting the consumption of protein-rich foods at breakfast and lunch, concentrating protein intake at dinner. The study by Barichella et al. (2017) demonstrated that PRD is associated with improved response to levodopa, with a reduction in motor fluctuations and the total required dose of the drug. It was also identified that daily protein consumption above the recommendation (0.8g/kg/day) was associated with higher doses of levodopa (Barichella et al., 2017). Recommendations for daily protein quantity and the redistribution pattern are supported by Brazilian and European guidelines for PD patients (Alves et al., 2023; Burgos et al., 2018).

Regarding the other macronutrients, the Acceptable Macronutrient Distribution Ranges (AMDRs) for adults will be used: carbohydrates will represent 45 to 65% and lipids 20 to 35% of the total caloric intake. For fiber, the Adequate Intake (AI) of 14 g/1000 kcal, which is based on energy consumption, will be used (Cominetti; Cozzolino, 2023).

| Nutrients     | Recommendations |
|---------------|-----------------|
| Energy        | EER (kcal/dia)  |
| Protein       | 0,8 g/kg/dia    |
| Carbohydrates | 45-65% do EER   |
| Lipids        | 20-35% do EER   |
| Fiber         | 14g/1000 kcal   |

### Telephone follow-up (D15 + D75)

To promote adherence to the recommendations and ensure complete follow-through, telephone calls will be made at D15 and D75 of the intervention to reinforce the guidelines and clarify doubts about the dietary plan.

Should a participant withdraw or not completely follow the protocol, the main study outcomes will be collected whenever possible, including data on constipation, diet, nutritional status, and clinical information. This data will allow for intention-to-treat analyses and reduce the impact of losses on the final outcome.

## 4.7 Assessments

### 4.7.1 Constipation

The evaluation of constipation will be performed using different instruments with the objective of capturing both subjective and objective aspects of bowel function:

#### 1. Evacuation Diary

All participants will receive an evacuation diary, which must be filled out daily during the study period. This instrument will allow monitoring the evolution of constipation symptoms throughout the intervention weeks. The registered information includes:

- Number of evacuations per week (evacuation frequency);
- Stool consistency using the Bristol Stool Scale, a validated visual tool that classifies stools into seven types. Types 1 and 2 will be considered hard stools, and their percentage will be calculated over time;
- Straining during evacuation (report of need to strain to evacuate);
- Sensation of incomplete evacuation;

- Use of rescue laxative (in case of absence of spontaneous evacuation).

## *2. Constipation Scoring System (CSS)*

The CSS will be applied at baseline, D45, and D90. This questionnaire consists of eight items and assesses the severity of functional constipation in adults, considering aspects such as frequency, effort, feeling of incomplete evacuation, and time spent on the toilet. Its total score allows for quantifying the intensity of the symptoms, assisting in monitoring the response to the intervention. The tool was translated, culturally adapted, and validated for the Brazilian population, demonstrating good comprehension by the patients and high psychometric reliability (Taniguchi et al., 2022).

### 4.7.2 Gut microbiota

Participants will receive instructions and the container for collecting the stool sample at baseline. The collection will be carried out by the participants themselves in their homes, following standardized instructions provided by the team. Participants will be asked to collect a portion from the inner part of the stool, using a spatula and a sterile container, and to keep the sample in a domestic refrigerator, if possible, for a maximum of 48 hours until delivery. This form of storage aims to preserve the integrity of the biological material until transport.

Transport to the laboratory will be carried out by the participant, if possible, in a maximum of one hour from the moment of removal from the refrigerator. The delivery of the sample will be arranged with the researchers, and this moment will be classified as D0. Upon arrival at the laboratory, the samples will be aliquoted into sterile microtubes and stored at -80°C until processing.

DNA extraction from the stool samples will be performed using a commercial kit (QIAamp PowerFecal Pro DNA Kit). The column extraction methodology will be based on the manufacturer's bacterial DNA extraction protocol. The final extraction product will be quantified and evaluated for the quality of the genetic material in each sample, for subsequent genomic library preparation.

The DNA obtained from the stool samples will be used for amplification of the hypervariable V3-V4 region of the bacterial 16S rRNA gene, by polymerase chain reaction (PCR), based on the 16S Metagenomic Sequencing Library Preparation Illumina® protocol. PCR will be performed with Phusion High-Fidelity PCR Master Mix with GC Buffer Enzyme (Invitrogen) and the Nextera XT Index Kit v2 Illumina will be used for DNA library preparation. All amplified PCR products will be purified using AMPure XP beads (Beckman Coulter). A negative control (molecular grade water) will be included for quality assurance. Library concentrations will be quantified using a Qubit DNA HS assay (Invitrogen) and checked for fragment distribution by a 4200 TapeStation System capillary electrophoresis instrument (Agilent). Pooled libraries will be loaded onto the MiSeq® platform using a

MiSeq™ i100 Series 25M Rgt Kit 600 cys reagent kit. These analyses will be performed at LABRESIS/HCPA.

- Fecal antigen test for *H. pylori*: A fecal antigen test for *H. pylori* will also be performed on the stool sample. It is a non-invasive exam that detects the presence of *Helicobacter pylori* in the feces through specific antibodies that identify bacterial antigens. It is used for the diagnosis of active infection and to confirm eradication after treatment.

#### 4.7.3 Diet

The dietary assessments (R24h and Screener-Nova) will be carried out with all participants at baseline, D45 (via telephone), and D90.

- 24-hour dietary recall (24hR)

The 24h recall (R24h) is a practical and widely used tool in nutritional studies to estimate habitual food intake. Its limitations, such as dependence on patient memory and representing only a single day of habitual eating, are known, meaning the R24h may not adequately reflect the variability of food consumption. However, it allows for quick collection of detailed information about the diet retrospectively, without interfering with eating habits. It is also a low-cost tool and well-accepted by participants.

Participants will be interviewed by a trained nutritionist, who will request the information in five steps: (1) quick listing of all foods and beverages consumed the day before; (2) detailed description of each item; (3) quantification using household measures and standardized utensils; (4) checking for forgotten items, such as the use of oil, condiments, and snacks; and (5) final review. Whenever possible, the use of photographs of household measures will be adopted to aid in the estimation of quantities. The collected information will later be analyzed using specific food composition software to calculate energy, macronutrients, micronutrients, and fiber.

- Diet quality

The diet will be assessed using the Screener-Nova. It is a self-administered food frequency questionnaire based on the Nova food processing classification, used to quickly monitor diet quality, with an average response time of 2 to 3 minutes, available on the QuestNova web platform, developed by the Center for Epidemiological Research in Nutrition and Health, at the University of São Paulo (NUPENS/USP) (Louzada et al., 2024). The researcher responsible for the assessment will apply the questionnaires with the participants to ensure better understanding.

The Screener-Nova is composed of seven blocks of yes/no questions, addressing food consumption from the previous day. Four of these refer to in natura or minimally processed foods

(fruits, vegetables, greens, and grains) and three assess ultra-processed foods (beverages, ready-to-eat meals, and snacks). The data automatically generate two indicators of diet quality, based on the simple sum of the items:

- Nova Whole Plant Foods (Nova-WPF), which ranges from 0 to 33 points and evaluates in natura/minimally processed foods.
- Nova Ultra-processed Foods (Nova-UPF), which ranges from 0 to 23 points and reflects the consumption of ultra-processed foods.
- Adherence to the nutritional intervention

Adherence to the nutritional intervention will be assessed through telephone calls and self-reported compliance with the guidelines, as well as the analysis of food consumption (24h recall). This monitoring will be carried out exclusively by the researcher responsible for the intervention and will be stored separately from the other data. Fiber consumption compared to the goals will be used as one of the indicators of adherence. Participants who meet at least 75% of the goals will be considered to have good adherence.

#### 4.7.4 Nutritional status

The assessments described below will be performed on all participants at the beginning and end of the study (baseline and D90).

- Anthropometry

Anthropometric measurements will be taken following the guidelines set out in the Technical Standard of the Food and Nutrition Surveillance System (Brasil, 2011). The measurements to be collected are: weight (kg), height (cm), calf circumference (CC), arm circumference (AC) and waist circumference (WC). The weight and height of the participants will be measured using a clinical scale with a stadiometer available in the CPC's consultation rooms. Circumference measurements will be taken with an inelastic tape in centimeters. Subsequently, the Body Mass Index (BMI) will be calculated by the ratio of weight (kg) to height (cm) squared. The BMI classification will be as follows: Underweight: BMI < 18.5kg/m^2; Normal weight: BMI between 18.5 and 24.9kg/m^2; Overweight: BMI between 25.0 and 29.9 kg/m^2; Obesity Grade 1: BMI between 30.0 and 34.9 kg/m^2; Obesity Grade 2: BMI between 35.0 and 39.9kg/m^2 and Obesity Grade 3: BMI ≥ 40.0 kg/m^2 (World Health Organization (WHO), 2000).

- Body Composition

Body composition will be evaluated using multi-electrode electrical bioimpedance (BIA), a non-invasive, safe, and widely used method in clinical and nutritional studies. The exam will be performed following standardized recommendations: minimum 4 hours fast, empty bladder, absence of intense physical activity in the last 24 hours, and no consumption of alcoholic and caffeinated beverages the day before. These guidelines will be previously agreed upon with the participants when signing the IC.

BIA uses a low-intensity electrical current applied through electrodes positioned on extremities (hands and feet), allowing for the estimation of the resistance and reactance of body tissues. From these measurements, various variables related to nutritional status and body composition will be obtained, including lean mass, fat mass, body fat percentage, body cell mass, total body water, estimated basal metabolic rate, segmental distribution of lean mass and fat, estimated visceral fat percentage, and phase angle.

- Nutritional Status Screening

Nutritional screening will be performed using the Mini Nutritional Assessment - Short Form (MNA-SF). This instrument consists of six multiple-choice questions, each related to a different domain, and corresponding to a score of 0-3 points. The questions are divided into changes related to the last three months and current moment questions. They cover the themes: decreased appetite, difficulty chewing and swallowing, weight loss, acute disease, mobility, dementia, BMI, among others. If it is not possible to measure BMI, the MNA-SF allows for the use of the CC value. At the end of the questionnaire, the points are summed, which will indicate: normal nutritional status (12-14 points), at risk of malnutrition (8-11 points), and malnourished (0-7 points) (Rubenstein et al., 2001).

- Sarcopenia Assessment

Sarcopenia assessment will be performed according to the revised European consensus in 2019 (Cruz-Jentoft et al., 2019) and classified as described in Figure 4 below. Firstly, the SARC-F screening tool will be applied. This questionnaire consists of five questions that address the participant's self-perception of their muscle function. Each question can be scored from 0 to 2, and the result can reach up to 10 points. Scores  $\geq 4$  are suggestive of sarcopenia (Woo; Leung; Morley, 2014).

Afterward, handgrip strength (HGS) will be assessed with a calibrated hydraulic dynamometer. To perform the measurement, the participant must be seated with their feet firmly supported on the floor and elbows at 90°. They will then be asked to squeeze the device as hard as they can, with 3 repetitions. The highest result in kilograms from the 3 attempts will be used for the classification of low HGS: <27kg for men and <16 kg for women. Subsequently, low appendicular skeletal muscle mass will be evaluated: <20kg for men and <15kg for women, obtained through the BIA exam.

Finally, the Timed Up and Go (TUG) test will be performed, which is a simple and quick method to assess mobility, balance, and fall risk. It consists of measuring the time an individual takes to stand up from a chair, walk three meters, turn around, and return to sit down. Low performance will be considered  $\geq 20$  sec.

#### 4.7.5 Sociodemographic data

The participants will answer a questionnaire developed by the researchers containing questions regarding personal and identification data of the participant such as age, sex, education, self-declared color, monthly family income, and about physical activity practice (APPENDIX C).

#### 4.7.6 Clinical data

Clinical data to be collected include: time since diagnosis, age at diagnosis, comorbidities, use of Deep Brain Stimulation (DBS) at the initial assessment (baseline). Disease staging using the Hoehn and Yahr scale, medications in use, daily equivalent levodopa dose (LEDD), and the following questionnaires will be applied both at baseline and at D90.

- Movement Disorder Society - Unified Parkinson's Disease Rating Scale (MDS-UPDRS)

The severity and impact of symptoms will be assessed using the MDS-UPDRS, a revised and widely validated version of the UPDRS scale. The application will be performed by a trained professional and will include the four parts of the instrument: Part I (patient's non-motor experiences of daily living), Part II (patient's motor experiences of daily living), Part III (motor examination performed by the evaluator), and Part IV (motor complications). Each item is scored on a scale from 0 (normal) to 4 (severe), and higher scores reflect greater impairment. This comprehensive assessment will allow for a detailed characterization of the participants' clinical status.

- The Montreal Cognitive Assessment (MoCA)

This instrument is used for screening patients with mild cognitive impairment. With a maximum score of 30 points, the MoCA assesses eight cognitive domains, contemplating various tasks in each domain such as: executive functions, visuospatial skills, naming, memory retrieval, digits, sentence repetition, abstract reasoning, and orientation. Its application takes about 15 minutes, and individuals who score more than 26 points will be classified as having mild cognitive impairment (Tumas et al., 2016).

- Swallowing Disturbance Questionnaire (SDQ)

The Swallowing Disturbance Questionnaire (SDQ) is a screening instrument developed to identify the risk of dysphagia in people with PD. It is composed of 15 questions that address symptoms

related to the oral and pharyngeal phases of swallowing. Fourteen items are answered on a scale of 0 to 3 (0 = never; 1 = rarely; 2 = frequently; 3 = very frequently), and one item is a dichotomous response (yes/no). The total score ranges from 0 to 45 points, with scores equal to or greater than 11 indicating a risk of dysphagia. The questionnaire has been translated and validated for Brazilian Portuguese, showing good reliability properties (Ayres et al., 2016).

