#### **3.2 Secondary Objectives**

1. To evaluate the effect of the nutritional intervention compared to the control on the intestinal microbiota composition of people with PD;
2. To relate the clinical aspects of PD with the intestinal microbiota composition;
3. To evaluate the food intake and diet quality of people with PD, as well as the effect of the nutritional intervention on these parameters;
4. To evaluate the nutritional status of patients with PD and the effects of the nutritional intervention on this outcome;
5. To identify the clinical characteristics associated with the effect of the nutritional intervention in patients with PD.

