#### 4.2.2 Exclusion criteria

Individuals who meet one or more of the following conditions will be excluded:

1. Diagnosis of atypical or secondary parkinsonism;
2. Hoehn and Yahr stage greater than 2;
3. Presence of severe neurological or psychiatric diseases that compromise the ability to participate in study procedures;
4. Diagnosis of previous dementia;
5. Presence of comorbidities such as active neoplasms, chronic obstructive pulmonary disease, heart failure and/or chronic kidney failure.
6. History of gastrointestinal neoplasms, inflammatory bowel diseases or surgeries involving the gastrointestinal tract;
7. Constipation secondary to clinical conditions, such as hypothyroidism or diabetes mellitus;

8. Opioid use;
9. Use of probiotics or antibiotics in the last 3 months;
10. Continuous use of laxatives in the last 8 weeks;
11. Presence of severe dysphagia according to the Functional Oral Intake Scale (FOIS) classification;
12. Individuals using enteral or parenteral nutrition;
13. Individuals receiving nutritional follow-up in the last 3 months.

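### The MoCA rule runs in the wrong direction: the best scores (27 to 30 of 30) are the ones classed as mild cognitive impairment

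*Protocol*

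**What the plan says.** Section 4.7.6 (Clinical data) introduces the MoCA by its purpose: "This instrument is used for screening patients with mild cognitive impairment". It then describes the construction: "With a maximum score of 30 points, the MoCA assesses eight cognitive domains, contemplating various tasks in each domain". The examples given include naming, memory retrieval, digits, sentence repetition, abstract reasoning and orientation. The paragraph ends with the rule for using the score: "individuals who score more than 26 points will be classified as having mild cognitive impairment". A study of the MoCA's validity in Brazilian patients with Parkinson's disease is cited for it.

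The MoCA is among the instruments covered by the statement that "the following questionnaires will be applied both at baseline and at D90", so the class can be derived twice per participant.

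No other part of the protocol restates, qualifies or corrects the rule.

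**The concern.** A test that awards points for cognitive tasks, up to a ceiling, gives its highest scores to the people who do best. A rule that calls the top of that range impaired therefore runs against what the score measures. The sentence is not background: it says how participants will be classified, and someone preparing the dataset could code it as it stands.

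Two things are at stake. The first is description. Section 4.8 plans frequencies and percentages for categorical variables, so a table of cognitive status would report the share of high scorers as the share with mild cognitive impairment. The second is interpretation. Secondary objective 2 relates clinical aspects of the disease to the microbiota, and secondary objective 5 is "To identify the clinical characteristics associated with the effect of the nutritional intervention in patients with PD". If the MoCA class were one of those characteristics, a benefit confined to cognitively intact participants would be reported as a benefit in the impaired. The analysis would run without any warning.

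**Working it through.** No sample size, power or error rate enters this point. The check is to list which scores fall in each class, compare this with the description of the instrument, and trace where the class could be used.

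**1. The rule as written.** Inputs from section 4.7.6: maximum 30, impaired if the score is above 26. Taking whole points from 0 to 30 gives 31 possible values.
- Labelled impaired: 27, 28, 29, 30, which is 30 − 26 = 4 values, including a perfect score.
- Not labelled: 0 to 26, which is 26 + 1 = 27 values, including zero.
- Check: 4 + 27 = 31.

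The protocol does not say in words that the 27 lower values are unimpaired. That is the complement of its rule.

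**2. The direction.** The protocol never states that a higher MoCA score is better. It follows from the description of a screen built from tasks such as memory retrieval and sentence repetition: under the rule, someone who completed every task would be impaired and someone who completed none would not. The protocol's other scales support this reading.

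| Instrument | What the protocol says | Direction |
|---|---|---|
| MDS-UPDRS (4.7.6) | "higher scores reflect greater impairment" | high is worse, stated |
| Swallowing questionnaire (4.7.6) | 11 or more means risk of dysphagia | high is worse, follows from the rule |
| Mini Nutritional Assessment, short form (4.7.4) | 12–14 normal, 0–7 malnourished | high is better, rule consistent |
| MoCA (4.7.6) | task-based, maximum 30; above 26 is impaired | high is better by construction, rule contradicts it |

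**3. Size of the misclassification.** Let the correct rule be: impaired if the score is below c. The written rule is: impaired if the score is 27 or more. The score values that get the same label under both rules are those lying between c and 27, and there are |27 − c| of them.
- c = 27 (26 counts as impaired): |27 − 27| = 0, so every score is labelled the wrong way.
- c = 26 (26 counts as normal): |27 − 26| = 1, so only a score of exactly 26 keeps its label.
- Each further point between c and 27 adds one score value that is labelled alike under both rules.

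The documents do not give c independently of the faulty sentence, so the first two lines hold only if 26 is the right number.

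**4. Effect on results that use the class.** Take c = 27, where the two classes are exact complements. If D = 1 marks true impairment, the written rule produces D* = 1 − D. A true proportion p is then reported as 1 − p. A regression coefficient or interaction b for D becomes −b for D*, with the same standard error. For other values of c the inversion is not exact, but the group called impaired is still the group with the higher scores.

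**5. Where the class enters.**
- Eligibility (4.2.2): no MoCA threshold. The cognitive exclusion is "Diagnosis of previous dementia".
- Primary outcome (4.4): weekly bowel movements from the diary. Not affected.
- Sample size (4.5): not affected.
- Model covariates (4.8): age, sex, disease duration and levodopa-equivalent dose. The MoCA is not listed.
- Secondary objectives 2 and 5 (3.2): refer to clinical aspects and characteristics in general, without naming the MoCA. Affected only if the class is used.
- Raw MoCA score: not affected.

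**The case against.** The strongest reply is that this is a slip of wording or translation in the description of an instrument, and that no planned analysis is shown to use the category. The score itself is collected from 0 to 30, section 4.8 provides summaries for quantitative variables, and a wrong label can be recoded at any time without loss. The direction is also partly inferred, because the protocol does not state that higher is better.

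Much of this stands, and it limits the point. A reader might infer that every participant ends up in the opposite class. That assumes 26 is the correct cut-off, which only the faulty sentence and an unseen source support. A reader might also infer that every association with cognition will be reported with the wrong sign. That holds only for analyses of the dichotomy, and neither objective 2 nor objective 5 names it. Nor do the documents support carrying the concern over to diary completion or adherence to the meal plan: the protocol mentions dependence on memory only as a limitation of the 24-hour recall. Modelling the score as continuous would avoid the problem, but that is an analysis preference and corrects nothing the protocol states.

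The reply does not rescue the sentence. The inference about direction is short, since the alternative is a screen for impairment that flags a perfect score and passes a score of zero. The text is a rule to be applied, and it is wrong as written rather than short of detail that an analysis plan would supply.

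**Conclusion.** The point holds in a limited form. The MoCA classification in section 4.7.6 is stated in the wrong direction: 4 of 31 possible scores, the highest, are called impaired, and the other 27 are unimpaired by complement. If the rule is applied literally, the proportion with mild cognitive impairment at baseline and day 90 is inverted, exactly so if the true boundary classes 26 as impaired. Any result under secondary objectives 2 or 5 that uses the class has its direction reversed.

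This rests on one inference, that points are earned by performing the tasks, which the protocol's description of the instrument supports. It does not rest on a remembered cut-off. It would be wrong to read it as a threat to the trial's main result: the primary comparison, who is enrolled, the sample size and the adjusted models as listed are the same with or without the error. It is a definite error of small reach, and it should be corrected before cognitive status is coded.

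**What to change.** In section 4.7.6, reverse the rule so that low MoCA scores are classified as mild cognitive impairment. At the same time, confirm two things in the validation study cited there: the cut-off value itself, and whether the boundary score counts as normal or impaired. State both explicitly, and carry the same definition into the coding of the variable at baseline and day 90.

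The cost is one corrected sentence and one look at a source the protocol already cites. Visits, instruments, data collection and sample size do not change, and any class already derived can be recoded from the stored scores.
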